#### 2.5.4. Cardiac Magnetic Resonance Imaging

CMR was performed at baseline and 6 months following randomization on a 3T scanner (ARCHITECT, General Electric, Milwaukee, Wisconsin, 53223, USA) equipped with a phased-array body surface coil and a cardiac-dedicated package with electrocardiogram gating. The following images were obtained within the study: conventional steady-state free-precession cine images covering the entire left ventricle on the short axis, with a slice thickness of 8 mm and no gap between slices, to calculate the indexed end-diastolic volume, indexed end-systolic volume, LVEF, and LV mass. T2 maps were obtained prior to contrast injection on the short axis. T1 maps were acquired before gadobutrol administration (0.2 mmol/kg, Gadovist^®^, Bayer Hispania, Barcelona, 08970, Spain) and 15 min later using a modified Look-Locker inversion-recovery sequence (MOLLI) with an embedded motion correction algorithm in the short-axis orientation at the basal, mid-ventricular, and apical levels, as well as in the four- and two-chamber views. Pre-contrast T1 maps were obtained using a 5-(3)-3 scheme, and post-contrast T1 maps were obtained with a 4(1)3(1)2 scheme. Late enhancement images were acquired 10 min after gadolinium administration using a standard ECG-gated T1-weighted segmented inversion-recovery gradient-echo sequence during repeated breath-holds in the same short axis locations and long axis views as for the cine images.

All scans were analyzed at a core laboratory facility (IDIBAPS Cardiac Imaging Group, Barcelona, 08006, Spain) by experienced cardiologists ([name] and [name]) in CMR postprocessing to generate a clinical report of the study. The scans were then pseudo-anonymized and analyzed by a single operator in accordance with the guidelines from the Society for Cardiovascular Magnetic Resonance and the European Society of Cardiovascular Imaging for reporting CMR examinations [11]. The baseline and 24-week scans were analyzed in pairs and side-by-side to minimize intra-observer variability, with the operator blinded to treatment allocation.

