### 2.6. Trial Outcomes

The primary, secondary, and exploratory outcomes will be measured as the change from baseline to 6 months of follow-up (Figure 1). Differences between the dapagliflozin and placebo groups in these changes will be analyzed. All CMR measurements will be indexed to body surface area, calculated at the time of the scan using the Mosteller formula.

*Primary outcome*

The primary endpoint is the change in ECV of the remote myocardium from baseline to six months, as measured by CMR.

*Secondary outcomes*

These include changes in the circulating biomarkers from baseline to six months: C-terminal propeptide of type I procollagen;N-terminal propeptide of type III procollagen;Galectin-3;High-sensitivity troponin I.

*Exploratory outcomes*

The exploratory outcomes include changes in other CMR measures of cardiac function and remodeling from baseline to six months, including: Left ventricular end-diastolic and end-systolic volumes;Left ventricular mass;Left ventricular ejection fraction.

They also include changes in other circulating biomarkers from baseline to six months and clinical events:N-terminal pro-B-type natriuretic peptide.Suppression of Tumorigenicity 2.Rate of major adverse cardiovascular events (MACE), including cardiovascular death, non-fatal myocardial infarction, non-fatal stroke, and heart failure hospitalization. All these endpoints will be adjudicated independently by a clinical event committee (CEC) (Supplementary Materials).Adverse events (AEs) and serious AEs were actively collected at follow-up visits and through spontaneous reporting by participants during the study. AEs of interest were represented by severe hypoglycemia, acute kidney injury, acute liver function profile impairment, severe dehydration, symptomatic and sustained hypotension, complicated genitourinary infections, diabetic ketoacidosis, and diabetic foot complications (in diabetic patients). AEs were recorded using a standardized form and assessed for severity, causality, and expectedness. All adverse events were communicated to the DSMB.Change in body weight from baseline to six months.

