## 3. Statistical Considerations

Based on previous studies conducted by this research group [2,4], it was determined that the change in the ECV of the remote myocardium, measured by cardiac magnetic resonance, between baseline and six months of follow-up in patients with STEMI was 1.5%, with a standard deviation of 2.2%. Assuming a change of 1.5% ± 2.2 in the ECV for the placebo group and an 85% relative reduction in the experimental group, the inclusion of 94 participants (47 per group) would have provided an 80% power to detect such a difference, with an alpha error of 0.05. To account for a 20% loss to follow-up and to ensure balanced groups for stratification based on two variables with two categories each, the final sample size was set at 120 participants (60 per treatment group). After premature termination of the study, a statistical power recalculation was conducted with the same assumption, finding that the final sample of 54 patients would provide 55% power to detect such a difference, with an alpha error of 0.05.

Analyses will be conducted on an intention-to-treat basis. The primary analysis will compare the mean change in ECV of the remote myocardium from baseline to six months between treatment groups (ΔECV dapagliflozin vs. ΔECV placebo) using Student’s t-test or a Mann–Whitney U test, depending on whether the variable has a normal distribution. In addition, a sensitivity analysis will be performed with a mixed model for repeated measures. Similar methods will be used for the analysis of secondary and exploratory outcomes, including changes in circulating biomarkers and other CMR-derived parameters. The mean differences will be reported along with 95% confidence intervals and two-sided *p*-values. Missing data will be handled by the last-observation-carried-forward methodology, while baseline missing data will be considered to be permanently missing. A detailed statistical analysis plan will be finalized prior to database locking and unblinding of the randomized groups.

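### Last observation carried forward turns every missing 6-month ECV into a change of exactly zero, because CMR is done only at baseline and 6 months

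*Protocol article*

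**What the plan says.** The missing-data rule is in Section 3 (Statistical Considerations): "Missing data will be handled by the last-observation-carried-forward methodology, while baseline missing data will be considered to be permanently missing". It stands in the same paragraph as the primary analysis, which compares the change in ECV between arms "using Student’s t-test or a Mann–Whitney U test, depending on whether the variable has a normal distribution". CMR outcomes are not exempted.

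Section 2.6 defines the endpoint: "The primary endpoint is the change in ECV of the remote myocardium from baseline to six months, as measured by CMR". Section 2.5.4 gives the timing of the scans: "CMR was performed at baseline and 6 months following randomization on a 3T scanner". Table 1 agrees: the visits at 1 and 3 months have no scan, and the 3-month visit has biomarkers only.

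Section 3 also gives the expected changes, "Assuming a change of 1.5% ± 2.2 in the ECV for the placebo group and an 85% relative reduction in the experimental group", and allows for 20% loss to follow-up. It adds: "In addition, a sensitivity analysis will be performed with a mixed model for repeated measures".

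Sections 2.5.3 and 2.5.6 try to obtain the follow-up CMR, where possible, from participants who stop treatment, deviate, start an open-label SGLT2 inhibitor or are withdrawn. Section 3 says a detailed SAP will be finalised before database lock and unblinding. Section 4.4 says no analysis has yet been done.

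**The concern.** With only two scan times, LOCF can do just one thing to a missing 6-month ECV: replace it with the baseline ECV. The change is then zero by construction. That contradicts the plan's own expectation in both arms, and by more on placebo, where ECV is expected to rise by 1.5 points.

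Two things follow for the primary result. The estimated difference moves away from the true 6-month difference. The imputed zeros are also counted as observed data and lower the standard deviation, so the interval is narrower than the scans actually obtained can justify. With 54 patients and a recalculated power of 55%, the estimate and its interval are the main product of this trial, so both need to be right.

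**Working it through.** **Inputs.** From Section 3: placebo change 1.5, SD 2.2, 85% relative reduction, two-sided alpha 0.05, 20% loss, final N = 54. From Section 2.5.1: 1:1 allocation. Assumed: 27 per arm, the same SD in both arms, scans missing at random within arm, and the t-test branch of the primary analysis. Differences are placebo minus dapagliflozin, in ECV points.

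**Reproducing the plan's figures.**
- Dapagliflozin change: 0.15 × 1.5 = 0.225. Difference: 1.5 − 0.225 = 1.275.
- n per arm = 2 × (1.960 + 0.842)² × 2.2² / 1.275² ≈ 46.7, so 47 per arm and 94 in total. The plan says "the inclusion of 94 participants (47 per group) would have provided an 80% power to detect such a difference, with an alpha error of 0.05".
- 94 / 0.80 = 117.5, so 118; the plan rounds up to 120.
- Power with 27 per arm (noncentral t): 55.2%; the plan states 55%.

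**Effect of LOCF.** If a fraction p of the 6-month scans is missing in an arm with mean change μ, the analysed change is a mixture of observed values and exact zeros:
- mean = (1 − p)μ
- variance = (1 − p)(2.2² + μ²) − [(1 − p)μ]²

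**20% missing in each arm.**
- Difference: 0.8 × 1.5 − 0.8 × 0.225 = 1.20 − 0.18 = 1.02.
- Placebo variance: 0.8 × (4.84 + 2.25) − 1.20² = 4.232.
- Dapagliflozin variance: 0.8 × (4.84 + 0.0506) − 0.18² = 3.880.
- LOCF SE: √[(4.232 + 3.880)/27] = 0.548.
- SE from observed scans (0.8 × 27 = 21.6 per arm): 2.2 × √(2/21.6) = 0.669.
- SE with nothing missing: 2.2 × √(2/27) = 0.599. LOCF thus reports more precision with a fifth of the scans lost than a complete data set would give.
- Coverage, normal approximation: the shift is 0.255/0.548 = 0.465 SE, so Φ(1.96 − 0.465) − Φ(−1.96 − 0.465) ≈ 0.925. Simulation (40,000 trials) gives 92.3%.

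**Range for equal loss, 27 per arm** (SEs by formula; coverage and power by simulation):

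| Missing in each arm | LOCF difference (true 1.275) | LOCF SE | Observed-scan SE | LOCF coverage | Power, LOCF / observed scans |
|---|---|---|---|---|---|
| 10% | 1.15 | 0.575 | 0.631 | 94.3% | 50.0% / 50.7% |
| 20% | 1.02 | 0.548 | 0.669 | 92.3% | 44.8% / 46.0% |
| 30% | 0.89 | 0.519 | 0.716 | 87.8% | 38.9% / 40.5% |

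Analysis of observed scans keeps coverage at about 95% throughout.

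**Unequal loss, no true effect (+1.5 in both arms).** The false difference is 1.5 × (p_dapagliflozin − p_placebo). The splits are assumptions; the documents give none.
- 20% and 20%: difference 0, type I error about 5%.
- 15% placebo, 25% dapagliflozin: 1.5 × 0.10 = 0.15; type I error about 6%.
- 10% placebo, 30% dapagliflozin (an assumed extreme): 1.5 × 0.20 = 0.30; type I error about 8.5%, against about 5% for observed scans.

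**Unequal loss, planned effect present.** The LOCF difference is 1.5(1 − p_placebo) − 0.225(1 − p_dapagliflozin).
- 30% placebo, 10% dapagliflozin: 1.05 − 0.2025 = 0.85, coverage about 87%.
- 10% placebo, 30% dapagliflozin: 1.35 − 0.1575 = 1.19, coverage about 95%.

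**The case against.** The best defence is that the harm may be small. Sections 2.5.3 and 2.5.6 pursue the follow-up scan after discontinuation or withdrawal, so losses may be well below 20%. At 10% in each arm coverage is still about 94%. With equal loss the test hardly changes: type I error holds at 5%, and power at 20% loss is about 45% with LOCF against 46% with observed scans. The SE is also accurate for the LOCF variable itself. It is too small only as a statement about the true 6-month change, and the undercoverage combines that with the bias. The SAP could still override the rule. All of this stands. It bounds the size, but it does not make zero a sensible value for a missing scan, and the article states the rule without exception.

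Four stronger readings are tempting but unsupported:
- *That biomarkers suffer in the same way.* Section 2.5.5 and Table 1 schedule a 3-month sample, which is normally the value carried. An exact zero arises only if that sample is missing too.
- *That LOCF contradicts the mixed model or makes it worthless.* A sensitivity analysis may rest on a different missing-data assumption, and Section 3 does not say the model is run on filled data. It does not say otherwise either, so one clarifying sentence is needed.
- *That leaving a missing baseline missing breaks intention to treat.* Sections 2.4 and 2.5.1 randomise only after a baseline CMR with LVEF at or below 50%. Only an unusable baseline ECV could drop a patient.
- *That type I error is generally inflated, or that LOCF is always conservative.* Inflation needs unequal loss, which nothing in the document predicts. Equally, unequal loss can produce a false benefit, so LOCF cannot be called safe.

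**Conclusion.** The concern holds for ECV and for the other outcomes measured only by CMR. As written, the rule gives a wrong primary estimate and an interval that overstates the information available. At the plan's 20% loss in each arm, the expected difference is 20% too small (1.02 against 1.275), the SE is about 18% below that from observed scans (0.55 against 0.67), and coverage is about 92%. Over 10% to 30% equal loss, the difference runs from 1.15 to 0.89 and coverage from about 94% to about 88%. Testing is affected mainly when loss differs between arms.

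These figures rest on 27 per arm, the plan's means and SD, the t-test, and scans missing at random within arm. The actual number of missing scans is unknown, and informative missingness was not examined.

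**What to change.** In the SAP, before lock and unblinding:
- Remove LOCF for ECV and the other CMR outcomes.
- Base the primary analysis on observed 6-month scans, using a likelihood-based model adjusted for baseline ECV, or multiple imputation within arm.
- Add a delta-adjusted sensitivity analysis that shifts the values assumed for missing 6-month scans and shows when the conclusion would change.
- State that the mixed model for repeated measures is run on unfilled data.
- Report the number of missing 6-month scans by arm.

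This takes about a paragraph and no new data. The price is a wider interval: at 20% loss, a mean width of about 2.70 points for a plain analysis of observed scans, against 2.19 under LOCF. Made after unblinding, the same change would look driven by the data.

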##### Native T1 and ECV Value Derivation

Whenever possible, three regions of interest (ROIs) of at least 1 cm^2^ were drawn in three distinct LV myocardial segments in the remote non-infarcted myocardium among the basal and midventricular slices, avoiding areas with image artifacts. Special attention was given to appropriate co-registration of the tracings between the baseline and follow-up studies to minimize interstudy variability and misregistration. The corresponding late-gadolinium enhancement short-axis images in the T1 maps were checked to avoid placing ROIs in areas with acute or chronic myocardial infarction. The mean values of all ROIs were labeled as the remote native T1 values for the baseline and follow-up studies. The mean myocardial ECVs for both baseline and follow-up studies were computed using the following formula:(1)$$ECV=\left(1-hematocrit\right)\times \left\lceil \frac{1}{Postcontrast\;T1my}-\frac{1}{Native\;T1my}\right\rceil ÷\left\lceil \frac{1}{Postcontrast\;T1bp}-\frac{1}{Native\;T1bp}\right\rceil$$
where postcontrast T1my is postcontrast myocardial T1; nativeT1my is native myocardial T1; postcontrast T1bp is postcontrast blood pool T1; and native T1bp is native blood pool T1.

LV Function, Volumes, and Infarct Size Calculations

Circle Cardiovascular Imaging 42 Medical Image post-processing software for Cardiac Magnetic Resonance, Version 5.12.1 (Calgary, Alberta, Canada), was used for these calculations. Briefly, an artificial intelligence-based algorithm automatically delineated the endocardial and epicardial contours at end-systole and end-diastole. Manual corrections were performed, if necessary, to compute the LV end-systolic and end-diastolic volumes and LVEF.

The infarct zone was quantified semi-automatically. Initially, the region with the highest signal intensity in the infarct core was identified, and the infarcted tissue was defined as the area with signal intensity above 50% of the maximum pixel intensity (full width at half maximum intensity method). Regions of microvascular obstruction were included in the quantification. Finally, the infarcted areas were summed and divided by the total mass of the left ventricular wall to calculate the infarct size as a percentage of the total LV mass.

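### Leaving missing baselines permanently missing while testing change scores drops any randomised patient without a usable baseline from that test, at a modest cost in precision

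*Protocol article*

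**What the plan says.** The missing-data rule is one sentence in section 3, Statistical Considerations. It fills other missing values by carrying the last observation forward and adds that "baseline missing data will be considered to be permanently missing". The same paragraph opens with "Analyses will be conducted on an intention-to-treat basis", with no qualifier.

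Section 2.6 defines the main outcome: "The primary endpoint is the change in ECV of the remote myocardium from baseline to six months, as measured by CMR". The biomarkers and the other CMR measures are also defined as changes over six months. Section 3 compares the arms "using Student’s t-test or a Mann–Whitney U test, depending on whether the variable has a normal distribution", uses similar methods for the secondary and exploratory outcomes, and adds that "a sensitivity analysis will be performed with a mixed model for repeated measures". It does not say whether baseline enters that model as a response or as a covariate. A detailed analysis plan is to be finalised before lock and unblinding, and section 4.4 says that no analysis has yet been done.

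**The concern.** The article does not leave the handling of missing baselines open; it fixes a rule. Combined with a change score, the rule leaves a patient with a real follow-up value and no baseline outside the t-test or Mann–Whitney comparison. That value is the outcome under randomised treatment, and sections 2.5.3 and 2.5.6 show the trial working to obtain follow-up scans even after patients stop treatment or leave the trial.

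A usable baseline is not guaranteed by eligibility. Section 2.4 requires a baseline CMR that yields an ejection fraction. ECV needs more: pre- and post-contrast T1 in myocardium and blood pool, plus hematocrit. Biomarkers need a separate blood sample. For a biomarker, both the three- and six-month values would go unused in the change analysis.

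At stake are the accuracy of the intention-to-treat label and some power in a trial that stopped at 54 of 120 patients.

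**Working it through.** **Inputs from section 3.** Placebo change and SD: "Assuming a change of 1.5% ± 2.2 in the ECV for the placebo group". With an 85% relative reduction, the difference is 0.85 × 1.5 = 1.275 points. Alpha is 0.05, taken as two-sided because section 3 reports two-sided p-values; allocation is 1:1.

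**Reproducing the plan's figures.** n per arm = 2 × (1.960 + 0.842)² × 2.2² / 1.275² = 46.7, so 47, as stated. With 27 per arm, power is 55.2% by the noncentral t and 56.7% by the normal approximation; the article states 55%. That figure takes all 54 patients as supplying a change score.

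**Power of the change-score test when patients without a baseline drop out** (noncentral t, losses split evenly; the counts are assumptions, since the article gives none):

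| Patients lost | Analysed | Power |
|---|---|---|
| 0 | 54 | 55.2% |
| 2 | 52 | 53.6% |
| 4 | 50 | 51.9% |
| 6 | 48 | 50.2% |

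The slope is (55.2 − 50.2) / 6 ≈ 0.8 points per patient. Losses of about 5%, 10% and 15% (51, 49 and 46 analysed) give 52.7%, 51.1% and 48.5%.

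**What a joint model recovers.** Let baseline and follow-up both be responses with common visit SD s and correlation ρ, and let the baseline mean be the same in both arms. Per arm there are c complete patients and m with follow-up only. The variance of the treatment difference is

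2s²(1 − ρ²) / [c + m(1 − ρ²)].

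A follow-up-only patient is thus worth (1 − ρ²) of a complete one; under the change-score test that patient is worth nothing. The proportional reduction in variance from keeping these patients is m(1 − ρ²) / [c + m(1 − ρ²)]. With 10% missing (m = 2.7, c = 24.3):

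- ρ = 0.4: 2.268 / 26.568 = 8.5%
- ρ = 0.6: 1.728 / 26.028 = 6.6%
- ρ = 0.7: 1.377 / 25.677 = 5.4%

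In power terms, fixing the change SD at 2.2 so that s = 2.2 / √[2(1 − ρ)] (normal approximation, ρ assumed), the joint model without and then with the follow-up-only patients gives:

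| ρ | 2 missing | 6 missing |
|---|---|---|
| 0.3 | 73.6% → 75.1% | 70.2% → 74.8% |
| 0.5 | 67.5% → 68.7% | 64.0% → 67.9% |
| 0.8 | 59.6% → 60.2% | 56.2% → 58.1% |

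Keeping the patients therefore adds 0.6 to 1.5 points with two missing and 1.9 to 4.6 with six. With none missing it adds nothing.

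**A separate gain from the same model.** With no baselines missing, its power is 75.2%, 69.1% and 61.2% at ρ = 0.3, 0.5 and 0.8, against 56.7% for the change score on the same approximation. That gain comes from adjusting for baseline and should not be credited to the missing-baseline clause.

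**The case against.** A reader might infer that these patients are discarded from the trial's analyses altogether. The text does not say so. It says that missing baselines stay missing; the loss follows only where a change score is tested. MACE and adverse events need no baseline value. The planned mixed model would keep follow-up-only patients if baseline were a response. It would lose them if baseline were a covariate, and the article does not say which. In either case it is only the sensitivity analysis.

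A reader might also infer bias, or a breach of randomisation. Neither is supported. Baseline is measured before treatment, and the scan reader is blinded to allocation, so absence of a baseline should not depend on arm. What fails is the unqualified label, for the patients concerned.

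The image-analysis section might be read as admitting that baseline ECV will sometimes be missing: "Whenever possible, three regions of interest (ROIs) of at least 1 cm^2^ were drawn". That phrase qualifies only how many regions are drawn; fewer than three still yield a mean.

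The design also guards against missing baselines. A baseline CMR gates randomisation, a full blood count and the biomarker sample precede it, and monitors checked completeness for every participant. No missing baseline is reported or expected. This stands, and it limits the size of the point. So does the paired, co-registered reading of scans: the article does not describe how a six-month ECV would be read without a usable baseline.

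Finally, leaving baselines unimputed in a change analysis is ordinary practice. That is fair, but the set should then be named for what it is. Carrying the last observation forward, in the other half of the same sentence, is a separate and weightier matter not judged here.

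**Conclusion.** The point holds in a limited form. For each change-score outcome, a randomised patient with a follow-up value and no usable baseline contributes nothing to the stated test, so the analysed set falls short of the declared intention-to-treat set by those patients. The cost is about 0.8 power points each from the stated 55%, on the plan's own difference and SD. How many there are is unknown: possibly none for ECV, more plausibly some for biomarkers. The power figures apply to ECV only, because the article gives no planning values for biomarkers. The recovery figures rest on assumed correlations and on equal visit SDs. The conclusion that there is no bias rests on a baseline's usability being judged without knowledge of arm. Correction is worthwhile because it is cheap and can still be made blind, not because the loss is large.

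**What to change.** In the analysis plan, before lock and unblinding, replace the clause by one of these:

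- Analyse baseline and follow-up values jointly as responses, with one baseline mean common to both arms and a treatment effect at each follow-up visit. This is a specified form of the mixed model already planned, moved from sensitivity to primary analysis.
- Use ANCOVA of the six-month value on baseline, with a missing baseline filled by the pooled mean computed without regard to arm, and the patient kept.

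If the change-score test is retained, describe its set as all randomised patients with a baseline value, report the number omitted by arm for each outcome, and state that baseline is a response in the sensitivity model. In each case, say how a follow-up scan is read when its paired baseline is unusable.

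The cost is model code and, for the first two options, a documented change to the primary-analysis wording. No new data are needed.
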